## Background

Adjustment disorder (AjD) refers to the clinical symptomatology that appears in response to an identifiable stressful event, such as separation or divorce, job loss, diagnosis of a disease, or family conflicts. In order for the diagnosis of AjD to be made, symptoms must begin within 3 months after the stressor and disappear within a period of not more than 6 months once the stressor or its consequences have terminated. Because the presence of an identifiable stressor is the key characteristic of this disorder, in the DSM-5 [1] AjD was classified under the new category of trauma and stress-related disorders. The same change has been proposed for the ICD-11, along with the proposal of a new diagnostic concept [2]. Despite these improvements, the category of AjD is not yet sufficiently clear [3] and a recent review study [4] revealed that there is still little support for the ICD-11 proposal of two symptom structure of AjD (preoccupation with a stressor or its consequences and failure to adapt).

According to the different studies carried out so far, AjD is a very common condition [3, 5, 6]. It is estimated to have an incidence of between 5 and 20% in mental health services, and about 50% in psychiatric consultation settings [1]. AjD is also one of the most frequent diagnoses in patients with organic diseases and surgical interventions [7–11], and in cases of absenteeism and work disability [12, 13]. In addition to being a highly prevalent disorder, AjD causes considerable distress and marked impairment in different functional areas of patients’ lives (e.g., family, friendships, school/work, etc.), and it may increase the risk of suicidal thinking and behavior [14, 15].

Despite these worrisome facts, little research has been conducted to identify and develop evidence-based interventions (EBI) for AjD. To the best of our knowledge, no specific EBI are available for AjD, just some suggestions and recommendations [3, 16]. Furthermore, only a few interventions for AjD have been assessed in a randomized controlled trial (RCT) [13, 17, 18]. Cognitive Behavioral Therapy (CBT) predominates in all of them, although other approaches are also included, such as the use of mindfulness.

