### Eligibility criteria

In order to be included in the trial, participants must meet the following inclusion criteria: (1) be 18 years old or more; (2) meet DSM-5 [1] criteria for AjD; (3) be able to understand and read Spanish; (4) be able to use a computer and have access to the Internet; (5) have an e-mail address. On the other hand, assessed participants who meet any of the following criteria will be excluded from the trial: (1) receiving another psychological treatment for AjD; (2) meet criteria for another severe mental disorder: alcohol or other substance abuse or dependence, psychotic disorder, dementia, or bipolar disorder; (3) meet criteria for a severe personality disorder or illness; (4) presence of risk of suicide or self-destructive behaviors. Undergoing pharmacological treatment is not an exclusion criterion during the study period, but any increase and/or change in the medication during the study period will imply the participant’s exclusion from subsequent analyses. A decrease in pharmacological treatment is accepted.

The decision about each participant’s inclusion or non-inclusion will be made by the entire clinical team, ensuring a more objective and reliable diagnosis. The telephone interviews will also be recorded, with the patient’s agreement, making independent inter-judge assessment possible.

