### Sample size

The sample size for the trial was calculated following the method described by Campbell, Julious, and Altman [37], and Freiman, Chalmers, Smith, and Kuebler [38]. G*Power 3 software [39] was used to facilitate power analysis.

Because there is no published research on the effectiveness of ICBT for the treatment of AjD, the sample size was calculated taking into account outcomes found in trials that used the BAI and BDI-II as measures of clinical change after an ICBT intervention in patients with clinical depression or anxiety disorder [40–42]. After reviewing the literature and adopting a more conservative approach, an effect size of .70 was assumed in the present study. Considering a significance level of 5% and a power of 80%, 26 participants in each group would be enough to detect the assumed difference. However, because the literature reveals dropout rates from ICBTs of around 30% [43], a sample of 68 participants will be recruited (34 per group).

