#### Waiting list control group

Participants on the waiting list group will be assessed before and after a period of 7 weeks. After completing a post-waiting period assessment, they will be offered the TAO program.

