### Support

Because the literature shows that guided ICBT provides better results than completely unguided interventions [45], all the participants will receive weekly phone support. This support will consist of a short phone call (maximum 10 min) during the intervention stage. The aim of these phone calls will be: 1) to clarify doubts about the use and functioning of TAO; 2) to remind them of the importance of continuing to work on the program contents; and 3) to congratulate them for their effort and achievements. Patients will receive up to 10 telephone calls over a 7–10 week period, and so they will have a maximum of 100 min of therapeutic support. No additional clinical content will be provided during the phone calls.

The support will be provided by experienced psychologists who will have at least a Master’s degree in Clinical Psychology. Before taking part in the trial, they will receive training in order to ensure that everyone provides the same support.

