### Assessment

Measurements will be taken at five different moments: baseline, post-intervention, and three follow-up periods (3-, 6- and 12-month). The diagnostic interviews will be administered by a trained clinician by phone. Moreover, all interviewers engaged in the assessment of potential participants will be supervised by a clinical team composed of mental health professionals with extensive experience in the diagnosis and treatment of stress-related disorders. Questionnaires will be self-administered online via the same virtual platform as the intervention program. Table 2 provides an overview of the measures used at each time point.

**Table 2 Tab2:** Study measures and assessment times

Assessment moment	Telephone assessment performed by a therapist	Automatic online assessment
BL	Diagnostic Interview for Adjustment Disorders, ADIS-IV-L*	BDI, Suicide item, BAI, ISL, PTGI, PANAS, MQLI
Post-M	–	Post-module assessment scale, suicide item
Post-M1	–	Post-module assessment scale, suicide item, Expectation of treatment scale
Post-T	Diagnostic Interview for Adjustment Disorders	BDI, Suicide item, BAI, ISL, PTGI, PANAS, MQLI, Opinion of treatment scale
FU	Diagnostic Interview for Adjustment Disorders	BDI, Suicide item, BAI, ISL, PTGI, PANAS, MQLI

*BL,* Baseline; *Post-M,* post-module; *Post-M1,* post-module 1; *Post-T,* post-treatment; *FU*, follow-ups; *ADIS-IV-L,* Anxiety Disorders Interview Schedule for DSM-IV: Lifetime Version; *BDI,* Beck Depression Inventory - Second Edition*; BAI,* Beck Anxiety Inventory; *ISL,* Inventory of Stress and Loss; *PTGI,* Posttraumatic Growth Inventory; *PANAS,* Positive and Negative Affect Scale; *MQLI,* Multidimensional Quality of Life Questionnaire; *** used only when differential diagnosis is needed

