#### Suicidal risk

The presence, frequency, and severity of suicidal thoughts will be assessed during the *Diagnostic Interview for Adjustment Disorders* administered by phone. The inclusion of a suicide item after each program module, at post-intervention, and at follow-up assessments will make it possible to detect participants who are at risk of suicide during the intervention and once the intervention is over.

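### Waiting-list participants have no scheduled suicide-risk check for 7 weeks, while TAO participants are asked after every completed module

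*Protocol article*

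**What the plan says.** - **Waiting list control group:** "Participants on the waiting list group will be assessed before and after a period of 7 weeks"; TAO is offered afterwards. The Abstract gives the same two assessment times.
- **Suicidal risk:** "The inclusion of a suicide item after each program module, at post-intervention, and at follow-up assessments will make it possible to detect participants" at risk while the intervention runs and after it ends. The section does not mention the waiting period.
- **Assessment, Table 2:** the suicide item appears at baseline, post-module, post-treatment and follow-up. The only entries between baseline and post-treatment are the two post-module rows, the general one reading "Post-module assessment scale, suicide item". The waiting list has no row of its own. On delivery, the section says "Questionnaires will be self-administered online via the same virtual platform as the intervention program".
- **Support:** weekly calls are promised to all participants, but "This support will consist of a short phone call (maximum 10 min) during the intervention stage". Their aims are help with using TAO, reminders and encouragement, and further clinical content is ruled out.
- **Eligibility criteria:** people are excluded for "presence of risk of suicide or self-destructive behaviors".
- **Background:** of adjustment disorder, the article says "it may increase the risk of suicidal thinking and behavior".

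**The concern.** The interim suicide check is attached to a treatment event, completion of a module. An arm with no treatment has no such event, so following the plan exactly leaves it without a check for the whole wait. The exclusion at entry describes each person's state on one day and says nothing about risk that develops later. Anyone receiving another psychological treatment for the disorder is also excluded, so at entry these participants have no other psychotherapist treating it who might notice a change.

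What is at stake is patient safety. Suicidal risk that arises during the wait may be found late, or missed if it resolves before week 7 or if the participant skips that assessment. A much smaller consequence is that risk detected between baseline and post assessment cannot be compared between arms, because only one arm is looked at.

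**Working it through.** The plan gives no figure of its own here, so the check is a count of scheduled contacts and a waiting-time calculation.

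**Inputs from the article**
- Wait of 7 weeks, with assessments at its start and end (Waiting list control group).
- Seven modules, numbered 0 to 6, taking about 7 to 10 weeks (Adjustment disorders online (TAO)).
- 34 participants per group, with 26 per group needed (Sample size).
- Dropout: "the literature reveals dropout rates from ICBTs of around 30" per cent (Sample size).

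**Assumptions**
- TAO participants complete modules at even intervals.
- Onset of risk is uniform over weeks 0 to 7.
- The post-waiting assessment uses the post-treatment battery of Table 2, including the suicide item.

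**Checks strictly between week 0 and week 7, per person**
- TAO, 7-week pace: completions at weeks 1, 2, …, 7, so 6 fall inside.
- TAO, 10-week pace: spacing 10/7 = 1.43 weeks, so completions at 1.43, 2.86, 4.29, 5.71 and then 7.14; 4 fall inside.
- Waiting list: 0.

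**Mean delay from onset to the next scheduled check**

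For a full gap of length g, the delay integrated over the gap is g²/2. Sum over the gaps and divide by 7.
- TAO, 7-week pace: 7 × (1²/2) / 7 = 0.50 weeks; maximum 1.0.
- TAO, 10-week pace: four full gaps give 4 × 1.43²/2 = 4.08. Onset between 5.71 and 7 is caught at 7.14 and gives (1.43² − 0.14²)/2 = 1.01. Then (4.08 + 1.01)/7 = 0.73 weeks; maximum 1.43.
- Waiting list: (7²/2)/7 = 3.5 weeks; maximum 7.
- Waiting list with weekly items in weeks 1 to 6 plus week 7: 0.50 weeks; maximum 1.0.

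**Arm totals inside the period**

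| | 7-week pace | 10-week pace |
|---|---|---|
| TAO, all 34 progress evenly | 34 × 6 = 204 | 34 × 4 = 136 |
| TAO, 10 of 34 complete no module | 24 × 6 = 144 | 24 × 4 = 96 |
| Waiting list | 0 | 0 |

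**Waiting-list participants who miss week 7**

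The article gives no loss rate for this arm. If the sample-size allowance applied, losses would be 34 − 26 = 8 (23.5%) to 0.30 × 34 = 10.2, about 10. Those 8 to 10 people would have no check after baseline in the randomised period.

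**The case against.** The strongest objection is that this is a condensed article. Crisis contacts and between-visit safety procedures usually sit in the full protocol, which an ethics committee approved and which is not shown. That stands as a limit: the article shows that no check is scheduled, not that risk goes unwatched by every route. It does not remove the point, because the assessment schedule is written out for both arms and the gap lies in what it states.

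Second, the asymmetry has a reason. The Discussion says that reprocessing the event can be very stressful, so checking after modules is sensible. This justifies checks in the TAO arm, but it does not justify having none in the untreated arm.

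Third, the exposure is limited: people at risk are screened out by interview, the clinical team decides on inclusion together, and the wait is short. This lowers the stakes without covering risk that emerges later.

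Fourth, several of the sizes rest on assumptions. TAO users may work at their own pace, and one who stalls also misses interim items. Treating 10 dropouts as completing no module is an extreme case. Applying an internet-therapy dropout rate to people who are waiting has no support in the article. These are fair criticisms of the arm totals and the loss figure; the count of 0 checks over 7 weeks depends on none of them.

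Finally, no between-arm analysis of suicidality is planned, so the trial's efficacy conclusions are unaffected. That is correct.

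**Conclusion.** The concern holds. As scheduled, each waiting-list participant has 0 suicide-risk checks between baseline and week 7, against 6 or 4 for an evenly progressing TAO participant. Under uniform onset the mean delay to the next check is 3.5 weeks against 0.50 or 0.73. The delay figures depend on even module progress and on the suicide item being part of the week-7 assessment. The article gives no rate of emerging risk, so harm cannot be quantified.

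This is a safety weakness in the schedule that should be corrected. It does not invalidate the design: comparison at baseline and post assessment remains possible. Confidence is medium, because an unseen full protocol could contain a procedure that covers the wait.

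**What to change.** Add a waiting-list row to Table 2, with matching text under Waiting list control group and Suicidal risk: the existing online suicide item is sent weekly in weeks 1 to 6, in addition to the week-7 assessment. State that the clinical team follows up a positive answer exactly as it does a positive post-module answer. The article does not describe that response, so the text should describe it or point to where it is set out. The TAO arm keeps its post-module item and needs no second weekly one. Confine any between-arm statement on suicidal risk to the baseline and post-assessment points common to both arms.

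Weekly is a choice; it matches the 7-week module pace. A single check at week 3.5 would cost less but leave a mean delay of 2 × (3.5²/2)/7 = 1.75 weeks and a maximum of 3.5.

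The cost is small: at most 34 × 6 = 204 automated presentations on the platform already used for questionnaires, a wording change and an ethics notification. The downsides are clinician time for positive answers and some extra contact with a control arm whose primary outcomes are self-reported depression and anxiety; a single item keeps that contact slight.

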### Support

Because the literature shows that guided ICBT provides better results than completely unguided interventions [45], all the participants will receive weekly phone support. This support will consist of a short phone call (maximum 10 min) during the intervention stage. The aim of these phone calls will be: 1) to clarify doubts about the use and functioning of TAO; 2) to remind them of the importance of continuing to work on the program contents; and 3) to congratulate them for their effort and achievements. Patients will receive up to 10 telephone calls over a 7–10 week period, and so they will have a maximum of 100 min of therapeutic support. No additional clinical content will be provided during the phone calls.

The support will be provided by experienced psychologists who will have at least a Master’s degree in Clinical Psychology. Before taking part in the trial, they will receive training in order to ensure that everyone provides the same support.

### Assessment

Measurements will be taken at five different moments: baseline, post-intervention, and three follow-up periods (3-, 6- and 12-month). The diagnostic interviews will be administered by a trained clinician by phone. Moreover, all interviewers engaged in the assessment of potential participants will be supervised by a clinical team composed of mental health professionals with extensive experience in the diagnosis and treatment of stress-related disorders. Questionnaires will be self-administered online via the same virtual platform as the intervention program. Table 2 provides an overview of the measures used at each time point.

**Table 2 Tab2:** Study measures and assessment times

Assessment moment	Telephone assessment performed by a therapist	Automatic online assessment
BL	Diagnostic Interview for Adjustment Disorders, ADIS-IV-L*	BDI, Suicide item, BAI, ISL, PTGI, PANAS, MQLI
Post-M	–	Post-module assessment scale, suicide item
Post-M1	–	Post-module assessment scale, suicide item, Expectation of treatment scale
Post-T	Diagnostic Interview for Adjustment Disorders	BDI, Suicide item, BAI, ISL, PTGI, PANAS, MQLI, Opinion of treatment scale
FU	Diagnostic Interview for Adjustment Disorders	BDI, Suicide item, BAI, ISL, PTGI, PANAS, MQLI

*BL,* Baseline; *Post-M,* post-module; *Post-M1,* post-module 1; *Post-T,* post-treatment; *FU*, follow-ups; *ADIS-IV-L,* Anxiety Disorders Interview Schedule for DSM-IV: Lifetime Version; *BDI,* Beck Depression Inventory - Second Edition*; BAI,* Beck Anxiety Inventory; *ISL,* Inventory of Stress and Loss; *PTGI,* Posttraumatic Growth Inventory; *PANAS,* Positive and Negative Affect Scale; *MQLI,* Multidimensional Quality of Life Questionnaire; *** used only when differential diagnosis is needed

#### Diagnostic interviews

##### Diagnostic interview for adjustment disorders

This interview will be used for the diagnosis of AjD and to check the fulfillment of inclusion/exclusion criteria. It is a semi-structured interview developed by our research group, taking into consideration the diagnostic criteria for AjD included in the DSM-IV-TR [46], the ICD-10 [47], and the *Structured Clinical Interview for DSM-IV (SCID-CV)* [48]*.* The first part of the interview aims to explore the presence of a stressful event (current or past). In order to make the interview easier, a list of 46 possible stressors is included. The second part includes 28 symptoms related to AjD. The presence and severity of these symptoms is rated on a 9-point scale (0 = Not at all; 8 = Very severe). The validation of this instrument is currently in process.

##### Anxiety disorders interview schedule for DSM-IV

*Lifetime Version (ADIS-IV-L)* [49]. This semi-structured interview will be used only when differential diagnoses with Generalized Anxiety Disorder and/or a Major Depressive Episode are needed. The ADIS-IV-L allows a reliable diagnosis of current and lifetime anxiety, mood, somatoform, and substance use disorders.

#### Primary outcome measures

*Beck Depression Inventory - Second Edition (BDI-II)* [50]*,* validated in the Spanish population [51]. The BDI-II is a widely used self-report inventory that measures characteristic attitudes and symptoms of depression. The total score is obtained by adding the scores on the 21 items that make up the instrument, with a maximum of 63 points. The instrument has good internal consistency (Cronbach’s alpha of 0.76 to 0.95) and test-retest reliability of around 0.8.

*Beck Anxiety Inventory (BAI)* [52], validated in the Spanish population [53]. The BAI measures the severity of both physiological and cognitive symptoms of anxiety. The 21 items are rated on a 4-point Likert-type scale (from 0 to 3), and the total score, which ranges between 0 and 63, is obtained after directly adding together the scores on all the items. Psychometric analyses carried out so far show excellent internal consistency (Cronbach’s alpha ≥0.85).

#### Secondary outcome measures

##### Inventory of stress and loss (ISL)

This inventory is an adaptation of the Complicated Grief Inventory [54]. It consists of 17 first-person statements about the degree to which the lost person/situation interferes in the individual’s life. There are 5 response options, ranging from 0 (“Never”) to 4 (“Always”). The validation of the instrument is currently in process. However, preliminary validation data [55] show excellent Cronbach coefficients in both general (0.91) and clinical AD (0.86) Spanish populations. Test-retest reliability was also excellent (0.90).

##### *Posttraumatic Growth Inventory (PTGI)* [56]

The PTGI is a 21-item instrument that assesses positive outcomes reported by individuals who have experienced traumatic events. A 6-point Likert response format is used, so that each statement is rated from “I did not experience this change as a result of my crisis” (scored 0), to “I experienced this change to a large degree as a result of my crisis” (scored 5). The instrument has excellent internal consistency (Cronbach’s alpha of 0.90) and acceptable test-retest reliability of around 0.71.

##### *Positive and Negative Affect Scale (PANAS)* [57]

The PANAS consists of 20 items that evaluate two independent dimensions: positive affect (PA) and negative affect (NA). The range for each scale (10 items on each) is from 10 to 50. The Spanish version has demonstrated high internal consistency (0.89 to 0.91 for PA and NA, respectively, in women, and 0.87 and 0.89 for PA and NA, respectively, in men) in college students.

##### *Multidimensional Quality of Life Questionnaire (MQLI)* [58]

This is a 10-item self-report instrument that assesses physical and emotional well-being, self-care, occupational and interpersonal functioning, community and services support, personal and spiritual fulfillment, and the overall perception of quality of life. Satisfaction in each of these areas is measured using a 10-point Likert rating scale. The MQLI is brief and easy to administer. It also presents good internal consistency (Cronbach’s alpha of 0.79) and a test-retest reliability index of 0.89.

#### Opinion measures

##### *Expectations and Treatment Opinion Scale* (adapted from Borkovec & Nau [59])

This self-report inventory measures patients’ expectations before they start the treatment and their satisfaction when they complete the treatment. The 6 items are rated from 1 (“Not at all”) to 10 (“Highly”) and provide information about the extent to which: 1) the treatment is perceived as logical; 2) patients are satisfied with the treatment; 3) the treatment would be recommended to a friend with the same problem; 4) the treatment would be useful to treat other psychological problems; 5) patients perceive the treatment as useful for their particular problem; and 6) the treatment is perceived as aversive. Participants will answer the Expectations scale after the therapist explains the rationale for the treatment they will receive and before beginning the treatment. The Satisfaction scale will be completed once the treatment ends. This adaptation has been used in previous studies [60–62].

